### h. Blinding

The study enforced rigorous protocols to maintain blinding among participants, research staff, and investigators regarding treatment allocation. The researcher responsible for receiving the tDCS device was unaware of whether it was programmed for active or sham stimulation, as an engineer handled this programming determined by randomization.

## i. Ethical guarantees for study participants:

The research was conducted by a team of trained physicians and psychologists based at the University Hospital of the Federal University of Rio Grande do Sul (UFRGS), Porto Alegre, Brazil. Patient triage will be performed by this team at the Hospital de Clínicas de Porto Alegre (HCPA), and clinical information will be collected with strict confidentiality. Participants will be thoroughly informed about all scientific and ethical aspects of the research in accessible language, tailored to their biopsychosocial context. They were enrolled in the study after providing written informed consent, with each participant retaining a copy of the signed document.

## j. Methods

The study protocol is outlined in the figure of timeline the study (**figure 2**), showing the assessments conducted at each stage.

The tDCS device used in the study was developed in collaboration with the Biomedical Engineering department of the Hospital de Clínicas de Porto Alegre (HCPA), Brazil. It is registered on the Brazilian National Health Surveillance Agency (ANVISA) under registration number N°80079190028. This device, designed for home use, has demonstrated its effectiveness in several trials .

Key features of the device include the ability to monitor contact impedance and automatically stop the session if impedance exceeds 1 mA for more than 5 seconds or if there is an electric current fluctuation greater than 10%. The device also logs the time and duration of each session, ensuring patient adherence. Since July 2020, it has been commercially available through Quark Medical (Brazil).

[figure not shown]

**Figure 2.** Timeline the study.

**Protocol Components:** The stimulation sites for the study include anodal tDCS with the anode placed over the left dorsolateral prefrontal cortex (DLPFC) (F3) and the cathode over the right DLPFC (F4). Additional components of the protocol involve pain education and physical exercise. The device features a high resistance and alarm system to adjust the cap and add saline, as well as monitoring curves of current intensity versus impedance for both active (a-tDCS) and sham (s-tDCS) stimulation.

**Assessments:** Participants completed a baseline questionnaire covering clinical and socio-demographic characteristics, analgesic use, heat pain threshold (HPT), and pain pressure threshold (PPT) assessed via quantitative sensory testing (QST).

**Instruments:** The study utilized several validated instruments, including the Fibromyalgia Impact Questionnaire (FIQ), Central Sensitization Inventory (CSI-BP), Beck Depression Inventory (BDI-II), Brazilian Pain Catastrophizing Scale (BP-PCS), Pittsburgh Sleep Quality Index (PSQI), and the Brazilian Portuguese version of the Profile of Chronic Pain: Screen (B-PCP).

## **The study's protocol consisted of a structured sequence:**

**Baseline Assessment:** This began at the center, where participants were initially assessed.

**Training Session (Visit 1):** Volunteers received comprehensive training on using the tDCS device correctly. They were provided with instructions for self-administration at home. The cap size and electrode positions were determined, and participants were given a link to a video guide for self-administration (<https://youtu.be/3Wtjj4esOGE>). They were also encouraged to contact the research team if needed.

**Visit 2:** Occurred four weeks after starting the tDCS protocol. Participants returned to the center for a treatment-end assessment and returned the device. Throughout the protocol, participants were required to use the device appropriately and keep records of any adverse effects experienced.

### **Cap Size and Electrode Positioning**

The process of determining cap size and electrode positions involved several steps:

- (i) Measuring the participant's head circumference to select the appropriate cap size (small, medium, or large).
- (ii) Participants wore the cap while the researcher identified electrode positions following the 10-20 EEG system.
- (iii) Electrode positioning on the cap was based on randomization, with scenarios such as anode at F3 and cathode at F4 (see Figure 1).
- (iv) Electrodes were inserted into vegetable sponges and secured in the cap following the 10-20 EEG system.
- (v) To avoid electrode placement errors, the anode was marked red, and the cathode was marked black.
- (vi) Detailed instructions for self-administration of the tDCS device at home can be found here: <https://www.jove.com/video/57614/home-based-transcranial-direct-current-stimulation-device-development>.

### **Training and Self-Application of tDCS at Home**

The training and instructions for participants to self-administer tDCS at home included the following steps:

- (i) Participants received initial training on equipment usage and skin irritation identification.
- (ii) The first treatment session was supervised with detailed instructions provided through a step-by-step video guide.
- (iii) Participants were instructed to prepare the stimulation area by exposing it in front of a mirror.

- (iv) The skin under the electrodes was cleaned with alcohol to remove creams, dirt, or grease.
- (v) Participants were guided to wear the cap, positioning the seam between their eyebrows.
- (vi) Approximately 6 ml of saline was added to the syringes connected to the sponges.

### ***HB-tDCS Sessions and Compliance Monitoring***

To ensure compliance with protocol during HB-tDCS sessions, we implemented several procedures:

- (i) Participants were advised to choose a quiet and suitable time in their daily schedule for their treatment session.
- (ii) The initial home-based session was conducted under remote supervision, allowing participants to seek assistance from the research team if needed.
- (iii) A weekly contact through WhatsApp to track participants' progress and ensure they adhered to the treatment protocol.
- (iv) Participants were encouraged to contact the research team for assistance.
- (v) Participants were instructed to promptly document any adverse effects in a diary following each tDCS home session.

To verify the adherence to the following protocol, a biomedical engineer reviewed the records to confirm the session time, duration, current intensity, and contact impedance. The average impedance was employed to assess the quality of the delivered current. The impedance should range between 8 and 4 k $\Omega$  at the beginning of stimulation, with the target during treatment between 3 and 2 k $\Omega$ . For a valid 20-minute a-DCS session, impedance levels should be between 3 and 2 k $\Omega$  for at least half the time in the case of a duration of 10 min. The literature supports the choice of a 10-minute duration by demonstrating its effectiveness in promoting neuroplasticity, with studies by Nitsche (2000)  and Bikson (2016)  adding to this understanding.

### **Exercises and Pain Science Education (PNE)**

One of the consequences of chronic pain is the fear of experiencing it and the avoidant behavior that immobilizes patients. This behavior hinders patients' active participation in treatment, which motivates the search for strategies that prioritize behavioral change to educate patients about the importance of their active involvement in alleviating symptoms and rehabilitating. Therefore, treatment includes strategies to modify coping capacity. Pain neuroscience education (PNE) programs aim to improve adherence and reduce fear and anxiety. PNE uses pain experience and associated consequences to clarify the neurophysiological-endocrine-immune-motor changes produced by pain to enhance the understanding of chronic pain as a disease, not a symptom. These programs aim to reframe individual perceptions of pain and make it less threatening, **empowering patients to take control of their pain management** . According to data from a systematic review with meta-analysis, which included qualitative and quantitative studies, PNE in chronic pain produces a clinically relevant effect in reducing kinesiophobia and pain catastrophizing .

PNE is presented through motivational interviewing to motivate participants to perform the proposed exercises and actively confront persistent pain and related symptoms. This model considers the role of beliefs and understanding

of one's disease (identity, cause, consequence, control, and duration) . A physical therapist supervises the implementation of videos on neuroeducation and exercise that are sent and made available via a mobile app. The orientation to perform the exercises is reinforced weekly through WhatsApp messages. The neuroeducation about pain was in a face-to-face evaluation on the day they received training to use the tDCS equipment, with questions directed at fear, cognitive distortion, and avoidance. This approach through motivational interviewing aligns with scientific evidence supporting the importance of the patient telling their own story regarding their pain experience, thus enabling a reconceptualization of chronic pain as a disease . The four videos address the following aspects:

**Video 1: Fibromyalgia as a mind-body syndrome** – managing symptoms and improving quality of life despite the lack of a cure (<https://youtu.be/37ULMvGDk3s>). Fibromyalgia is a chronic pain syndrome marked by widespread pain, fatigue, sleep disturbances, and cognitive issues, primarily affecting women and significantly reducing quality of life. It stems from altered brain pain regulation, heightening pain sensitivity. Though incurable, a multimodal treatment approach can help manage symptoms: (i) Medications alleviate pain and improve sleep but do not eliminate symptoms. (ii) Physical exercise may reduce pain, enhances mobility, and builds strength. (iii) Complementary therapies, like tDCS show promise as adjunctive treatments. Therefore, a comprehensive care plan empowers patients to better manage symptoms and enhance their quality of life.

- **Video 2: Fibromyalgia and central sensitization** – how the loss of inhibitory capacity makes the brain more sensitive to pain (<https://youtu.be/MpSNGLTs5Wk>). The video aim to give insights for patients about fibromyalgia as a complex condition marked by widespread pain, fatigue, sleep disturbances, and mood changes, due to central sensitization, where the brain becomes overly sensitive to pain. The brain loses its ability to inhibit pain, intensifying discomfort. Managing symptoms effectively involves strategies like physical exercise and tDCS, which stimulates the brain to reduce pain. Combining these treatments with professional guidance is essential for better symptom control and improving quality of life.
- **Video 3: Fibromyalgia as a chronic pain condition characterized by dysfunction of the central system** – stressors exacerbate symptoms, but focusing on quality of life and active participation in treatment enhances outcomes (<https://youtu.be/oJOpurJRJQ4>). Effective management requires a multimodal approach, including: (i) Regular Exercise improves physical function and reduces pain. (ii) Education helps identify and manage triggers. (iii) tDCS therapy enhances treatment effectiveness.
- **Video 4: Exercise program** – strengthening, flexibility, and aerobic activities to be performed before each tDCS session (<https://youtu.be/l95-5YwgFeE>). This video provides a Complete Guide with detailed instructions on exercises

to complement tDCS sessions for fibromyalgia. The recommended program includes strengthening exercises for the upper and lower limbs and axial regions using body weight, functional movements, and alternating limb exercises. Key exercises include squats (sitting and standing from a chair) and bilateral plantar flexions. Flexibility is addressed through stretching targeting the upper and lower limbs, lumbar, and cervical spine. The program includes two blocks of five exercises, with at least two sets, adjusted based on fatigue and pain levels. Exercises are performed daily before tDCS sessions for 15–20 minutes, complemented by aerobic walking 2–3 times per week based on tolerance.

- **Exercise Program for Study Participants**

1. Seated, elbow flexion, palms up.
2. Seated, knee extension, one at a time.
3. Seated, shoulder flexion, sagittal plane, bilateral.
4. Standing, hip flexion 90°, one at a time.
5. Standing, hip abduction, one at a time.
6. Standing, shoulder abduction, coronal plane, bilateral.
7. Standing, bilateral plantar flexion.
8. Sit and stand from a chair (minimum of 43 cm from the ground).
9. Cervical region mobility – flexion and extension, rotations, and inclinations.
10. Trunk mobility – flexion and extension, rotations, and inclinations.
11. Deep diaphragmatic breathing technique.

## **Instruments and Assessments**

The tools used to measure psychological and clinical outcomes were validated in the Brazilian population. The schedule of assessment is presented in Table 1.

### **Primary Outcome**

- i. Pain interference was assessed using a multidimensional pain score from the Brief Pain Inventory (BPI), which evaluates seven daily activities: general activity, walking, work, mood, enjoyment of life, relationships, and sleep. BPI pain interference scores range from 0 to 10, with 0 indicating no interference and 10 indicating complete interference. Overall pain interference was calculated as the mean of the seven items. The assessment was conducted over a 4-week treatment period and at three months of follow-up .

### **Secondary Outcomes:**

- ii. The Brief Pain Inventory (BPI) assesses pain at its “worst,” “least,” “average,” and “now” (current pain) on a 0–10 numerical rating scale, where 0 indicates no pain and 10 represents the worst pain imaginable. This assessment was conducted weekly during treatment and three months after treatment completion. These single-item measures are supported by IMMPACT recommendations for pain assessment in clinical trials  and the FDA Draft Guidance for Patient-Reported Outcome Measures .
- iii. The Brazilian Profile of Chronic Pain: Screen (B-PCP) identifies the individual's multidimensional pain experience across three domains: pain severity (0-32), disability (0-36), and emotional burden (0-25). Higher scores indicate

- greater disability or emotional distress, with a total score ranging from 0 to 93 points. Changes from baseline to the end of treatment and at three months follow-up will be analyzed.
- iv. Fibromyalgia Impact Questionnaire (QIF): Measures the impact of fibromyalgia on quality of life across three domains: function (9 questions), overall impact (2 questions), and symptoms (10 questions). Scores are weighted differently, with a maximum total score of 100 .
  - v. Patient Global Impression of Improvement (PGI-I): A 7-point scale assessing patients' perceptions of symptom improvement post-treatment, ranging from "very much worse" (1) to "very much improved" (7) . Impressions were categorized into "improved" or "very much improved" versus "very much worse" to "slightly improved".
  - vi. Quantitative Sensory Testing (QST) is a standardized protocol using a computer Peltier-based device thermode (measuring 30X30mm), which was attached to the skin on the ventral aspect of the mid-forearm. The temperature was set at 32OC and increased at a rate of 1 OC/s until it reached a maximum of 52Oc. Each participant was instructed to push the button when the stimulation became painful. To determine the heat pain threshold, each patient's threshold was measured three times, with a 40-second break between each assessment. The average of the three assessments was used to define the heat pain threshold for each patient .
  - vii. The endogenous pain modulatory system (EPMS) function was assessed through a conditioned pain modulation (CPM) test using a computerized thermode, like the one used to determine the heat pain threshold (HPT). Initially, on the non-dominant forearm, three quantitative sensory testing (QST) assessments were conducted with a 40-second interval between stimuli. Each participant was instructed to press a button when their numerical pain score (NPS, 0-10) reached 6/10. The average temperature of the test stimulus was recorded as T0. After five minutes, participants immersed their dominant hand up to the wrist in water at a temperature of 0°C–1°C for 15 seconds. The QST was then reassessed, resulting in a pain score NPS(T1) based on the evoked pain from the thermode using the T0 temperature on the ventral non-dominant forearm. The CPM test score was calculated as the difference between NPS(T1) and NPS(T0). A negative CPM score indicates proper EPMS function, while a score of  $\geq 0$  indicates impaired function.
  - viii. Side effects of tDCS were evaluated using the Systematic Assessment for Treatment Evaluation questionnaire.
  - ix. Adherence to the protocol was assessed by the record in the tDCS device, which registers impedance, resistance, time of use, and duration of each session. This data was downloaded at the end of the treatment.

### **Clinical Measurements: Included assessments of depressive symptoms, central sensitization, sleep quality, analgesic use**

- x. Demographic Data and Medical Comorbidities: Collected via a standardized questionnaire.
- xi. Psychological Assessments: Included the Pittsburgh Sleep Quality Index (PSQI)  and the Central Sensitization Inventory for the Brazilian Population (CSI-BP)  with scores indicating symptom severity. Depressive symptoms were assessed using the Beck Depression Inventory II, and the Pain Catastrophizing Scale (PCS) evaluated catastrophic thinking about pain .

- xii. Analgesic Use: Patients were allowed to take additional medications as needed and were instructed to record their intake in diaries. The total dose taken each week during the treatment period and three-month follow-up were used for analysis.

### Schedule of assessment.

|                                                                      | Baseline | Week1 | Week2 | Week3 | Week4 | 3-month follow-up |
|----------------------------------------------------------------------|----------|-------|-------|-------|-------|-------------------|
| Sociodemographic and lifestyle questionnaire                         | X        |       |       |       |       |                   |
| 2016 American College of Rheumatology Diagnostic Criteria (ACR-2016) | X        |       |       |       |       |                   |
| Central Sensitization Inventory                                      | X        |       |       |       |       |                   |
| Pain Catastrophizing Scale                                           | X        |       |       |       | X     |                   |
| Beck Depression Inventory (BDI-II)                                   | X        |       |       |       | X     |                   |
| Pittsburgh Sleep Quality Index (PSQI)                                | X        |       |       |       | X     |                   |
| Outcomes                                                             | X        |       |       |       |       |                   |
| Brief Pain Inventory (BPI)                                           | X        | X     | X     | X     | X     | X                 |
| Patient Global Impression of Improvement (PGI-I)                     |          |       |       |       | X     |                   |
| Fibromyalgia Impact Questionnaire (FIQ)                              | X        |       |       |       | X     |                   |
| Conditioned Pain Modulation (CPM-test)                               | X        |       |       |       | X     |                   |
| Side effects of tDCS questionnaire                                   |          |       |       |       | X     |                   |

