## Statistical Analysis

Continuous and categorical variables were compared using Fisher's exact test, the chi-square test, and the t-test for independent samples. The Shapiro-Wilk normality test was applied to determine the normal distribution of continuous variables. A Linear Mixed-Effects Regression Models for Repeated Measure (LMM) assessed primary outcomes (pain severity and disability) with treatment, placebo response (responder vs. non-responder), time, and the treatment-by-time interaction as fixed effects, and included a random intercept for patients to account for time differences. If appropriate, we then performed the Bonferroni's Test adjustment for post hoc multiple comparisons to identify differences between the groups at each time point and used a paired t test to assess the effects on each experimental group. The Generalized Linear Model (GLM) was used to examine the treatment effect on the secondary outcomes including quality of life, HPT, PGI-I and the descending pain inhibitory system (DPIS). The treatment effect on primary and secondary outcomes was adjusted for analgesic use and placebo susceptibility. Analgesic use was included in the model to control a potential confounder affecting pain outcomes. This ensures that the observed effects of a-tDCS and s-tDCS are attributable to the interventions rather than variations in analgesic use, thereby enhancing the validity of the results. All analyses were adjusted for multiple comparisons using Bonferroni's Test. The modified ITT (m-ITT) analysis included those completing  $\geq 50\%$  of sessions, with missing data imputed using regression model coefficients. In the m-ITT, with an adjusted protocol, encompassing all patients who completed at least ten sessions. The choice of ten sessions for ITT was guided by most of the literature supporting clinical symptom improvement in chronic pain. This method is not as strict as classical ITT, but it suggests that A-tDCS could be useful in clinical settings with at least a minimum number of sessions. Specifically, we replaced missing values with imputed data derived from a regression model using observed data. The treatment group served as the predictor, and the outcome variable with missing values was imputed based on regression coefficients, indicating the relationship between the treatment group and the outcome. This imputation method was applied, for example, to ten patients who withdrew after ten tDCS sessions. Sensitivity analyses confirmed consistent LMM results with or without imputation ([see per-protocol analysis in results - Supplement II](#)).

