## Risks and Benefits of the Study:

**The study involved minimal risk.** The two procedures—multisession (a-tDCa) targeting the PFC, combined with exercise (E) and pain education (PEN)—had been previously studied in home settings, with no reports of serious complications or brain damage. tDCS used a low-intensity current, which was safe for fibromyalgia, with the most common side effect being mild scalp tingling, minimized by humidifying the electrodes with saline.

The main benefit for participants was the potential improvement in pain-related symptoms of fibromyalgia. Participants could also join a 3-month follow-up phase, where a-tDCS -E-PEN was offered in an open phase. Although the study took

place at home, patients visited the research center for periodic clinical evaluations and had remote access to the research team for questions and updates. Any clinical complications were treated at the Hospital de Pronto Socorro, Porto Alegre, Brazil, with treatment provided free of charge as needed.

After the study, participants were referred back to their original outpatient clinics with appropriate prescriptions and care instructions

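### The structured side-effect questionnaire is scheduled only at Week 4, with no baseline, early-stopping or 3-month administration, and the adverse-effect diaries are not tied to the side-effect evaluation

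*Protocol*

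**What the plan says.** **The structured instrument.** Secondary Outcomes, item viii, states: "Side effects of tDCS were evaluated using the Systematic Assessment for Treatment Evaluation questionnaire". It gives no timing. The timing is in the Schedule of assessment, where the row "Side effects of tDCS questionnaire" has one mark, at Week 4. The cells for Baseline, Weeks 1 to 3 and the 3-month follow-up are empty, and the 3-month column contains only the BPI.

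**The visits.** In the structured sequence of the study, the only visit after training is Visit 2, which "Occurred four weeks after starting the tDCS protocol". The device is returned then. No visit or assessment is described for a participant who stops before that.

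**Other recording.** The section on HB-tDCS sessions and compliance says: "Participants were instructed to promptly document any adverse effects in a diary following each tDCS home session". The visit sequence likewise asks participants to "keep records of any adverse effects experienced". The same compliance section provides "A weekly contact through WhatsApp to track participants' progress and ensure they adhered to the treatment protocol".

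**The open phase.** Risks and Benefits describes a 3-month follow-up phase "where a-tDCS -E-PEN was offered in an open phase". It does not limit this to one arm. It also mentions clinical evaluations at the centre, remote access to the team and free treatment of complications. The Study Discontinuation Criteria apply whenever a problem arises.

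**Withdrawals.** Statistical Analysis gives, as an example of where imputation was used, "ten patients who withdrew after ten tDCS sessions".

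**The concern.** A questionnaire given once, at the end of treatment, leaves three gaps in the structured safety data.

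- **No baseline.** Headache, depression and abdominal pain appear in the Inclusion Criteria as features of the condition. A symptom reported at Week 4 may have been there before the first session.
- **No administration at early stopping.** Someone who leaves before Week 4 has no scheduled occasion to complete the form. If some of these people stop because they tolerate stimulation poorly, the form misses those it most needs to reach.
- **Nothing structured in the open phase.** Active stimulation is on offer there, and the Schedule of activities plans a separate analysis of open-phase data, yet no side-effect form is scheduled at the 3-month contact.

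At stake is the trial's statement on side effects. It would describe Week 4 attenders in the blinded phase, without separating new from pre-existing complaints.

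**Working it through.** **1. The denominator.** The point does not depend on the sample-size calculation, but it uses the total of 112, so that was checked. The inputs are in the sample size section: difference 0.6, SD 1, 80% power, 5% level (two-tailed by Statistical Analysis), autoregressive correlations 0.4 and 0.2, and retention of 99, 98, 96 and 94% at moments 2 to 5.

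n per arm = (φa + φb)(z0.975 + z0.80)² SD² / δ², where φ is the variance factor at the last moment given correlation and attrition. With φa = 1.060 and φb = 1.063, n = 46.3, rounded up to 47 (94 in all). Then 47 / 0.85 = 55.3, rounded up to 56 per arm, or 112. The Protocol's figures reproduce.

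**2. What is collected, and when.**

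| Situation | Questionnaire | Other provision |
|---|---|---|
| Before treatment | none | BDI-II and comorbidity questionnaire, no side-effect form |
| Home sessions, blinded phase | none until Week 4 | diary after each session; weekly contact for progress and adherence |
| Stopping before Week 4 | none | diary up to stopping; retrieval not described |
| Week 4 | yes | device returned |
| Open phase and 3 months | none | general oversight; the diary instruction is not limited to the blinded phase |

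**3. Do the diaries feed the evaluation?** Compare two diaries. For analgesics (Clinical Measurements, item xii), the Protocol says that the weekly totals, through treatment and the three-month follow-up, are used for analysis. For adverse effects, it says that entries are made but not how they are collected from people who leave, or whether they are analysed. Item viii names only the questionnaire as the means of evaluation.

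**4. How many could miss the form.**

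- At 94% retention: 0.06 × 112 = 6.7, about 7.
- At the planned 15% dropout: 0.15 × 112 = 16.8, about 17.
- Reported withdrawals after ten sessions: 10 / 112 = 8.9%, if all 112 were randomised.

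The first two are upper figures. The 94% applies to moment 5, which the sample size section places three months after treatment, so some of those losses may fall after Week 4. On the third, Statistical Analysis treats ten sessions as half the course, which implies about 20. The ten patients therefore seem to have left in the second half of treatment. They are not split by arm, and nothing says whether they completed the form.

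**5. What the missing baseline does.** Let p be the share of an arm with a symptom before treatment that persists, and q the share of the others who develop it. The Week 4 rate is p + (1 − p)q.

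- Within an arm, this exceeds the rate of new symptoms, (1 − p)q, by p.
- Between arms, randomisation makes p equal in expectation, so the difference is (1 − p)(qA − qS). Pre-existing symptoms create no false difference. A worsening of a symptom already present goes uncounted, however, and differential loss before Week 4 could still disturb the contrast.

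The Protocol gives no value for p, so the within-arm excess cannot be quantified.

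**The case against.** The strongest reply is that side effects are recorded far more often than the schedule row suggests. A diary entry is asked for after each home session, so a participant who stops early should have a record up to that point. This stands: a reader might infer from the single mark that side effects are asked about only once, and that would be wrong. It is true of the questionnaire alone.

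A reader might also infer that open-phase participants have no safety assessment. The Protocol does not support that. It describes clinical evaluations, remote access and a discontinuation rule without a time limit, and the schedule table does not mention the open phase by name. What is absent is a scheduled, structured side-effect assessment. That sham participants receive their first active course there is likewise an inference: the text neither states nor excludes it.

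On the baseline, the reply is that a concurrent sham arm carries the same background symptoms and that depression is measured at baseline by the BDI-II. Both are correct, and they limit the gap mainly to rates within an arm and to the open phase, which has no described comparator. The questionnaire itself is not shown. It may ask about onset or attribution, which would narrow the gap further.

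Finally, counting rules and the safety population often belong in a SAP. That is fair for those details. The timing of the questionnaire, however, is fixed in this Protocol, and a SAP cannot recover answers that were not collected.

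**Conclusion.** The concern holds in a limited form. The only structured side-effect instrument is scheduled once, at Week 4, without a baseline, an administration on early stopping or one at 3 months. Diaries and general oversight exist, but the document does not connect the diaries to the side-effect evaluation.

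The consequence is that questionnaire-based rates within each arm mix old and new symptoms and may omit early stoppers: about 7 of 112, up to about 17, both upper figures. This assumes that the schedule was followed as written and that no unscheduled form was given on withdrawal. The between-arm contrast is partly protected by the sham control.

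It is tempting to go further and conclude that active stimulation will look better tolerated than it is. The documents do not support a direction: withdrawals are not given by arm, and no reasons for them are stated. Nor can the 3-month period be counted as time without any side-effect collection. Participants who did not join the open phase are not described as receiving stimulation then, and for those who joined, the diary instruction is not expressly excluded.

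**What to change.** In the Schedule of assessment, add the same questionnaire:

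- at baseline, before any stimulation;
- at device return whenever stimulation stops early;
- at the existing 3-month contact.

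Count as side effects those that are new or worse than at baseline. Tabulate everyone who had at least one session, using diary entries where the questionnaire is missing, and say so in item viii. Report open-phase events separately, by original arm.

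The cost is a schedule amendment and a short form, with small added patient burden. Baseline and 3-month contacts already exist; only the early-stopping administration is a new occasion.

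Much of the Protocol is in the past tense, so collection may already be complete and a baseline form no longer possible. In that case, retrieve the diaries, including those of participants who withdrew, state the questionnaire denominator by arm, and limit the safety statement to what those data cover.
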